# Comparison of amiodarone and esmolol for prevention of reperfusion ventricular fibrillation in individuals undergoing heart valve or aortic surgery: a study protocol for a randomized controlled clinical trial

**DOI:** 10.1186/s13063-023-07816-w

**Published:** 2023-11-27

**Keywords:** Amiodarone, Esmolol, Reperfusion ventricular fibrillation, Blood drainage volume

## Abstract

**Background:**

Amiodarone and esmolol can help to prevent and treat post-cardiac surgery reperfusion ventricular fibrillation. However, the relative efficacies of these two drugs remain unknown. The aim of the current trial is to compare the performances of amiodarone and esmolol for preventing reperfusion ventricular fibrillation following open heart surgery.

**Methods/design:**

This is a single-center, prospective, double-blind, controlled clinical trial. A total of 260 patients undergoing heart valve or aortic surgery will be assigned randomly to treatment with prophylactic esmolol (intervention group) or amiodarone (control group). The main outcome is the incidence of reperfusion ventricular fibrillation following aortic opening during extracorporeal circulation. The secondary outcomes are the rate of automatic cardiac resuscitation, energy and frequency of electrical defibrillation, number of electrical defibrillations, and pacemaker use in the two groups of patients. Information on the patients’ general condition and the durations of anesthesia, extracorporeal circulation, aortic occlusion, and operation time will be recorded. We will also compare the heart rate, mean arterial pressure, and central venous pressure between the two groups of patients at induction of anesthesia (T1), start of surgery (T2), start of extracorporeal circulation (T3), aortic block (T4), aortic opening (T5), after opening for 10 (T6), 20 (T7), and 30 min (T8), at cessation of extracorporeal circulation (T9), and at the end of surgery (T10) and compare blood gas analysis results at T1, T5, T9, and T10.

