## Interventions

### General anesthesia

All patients will receive conventional general anesthesia as follows: induction with midazolam 0.05 mg/kg, etomidate 0.3 mg/kg, sufentanil 0.5 µg/kg, and cis-atracurium 0.2 mg/kg. The anesthesia machine is connected after tracheal intubation, the tidal volume is set at 6–8 mL/kg, and the respiratory rate is 12 breaths/min. The intraoperative end-tidal CO_2_ pressure is maintained at 35–45 mmHg by adjusting the respiratory parameters, and the bispectral index (BIS) is maintained at 40–60. Anesthesia will be maintained with continuous pumping of propofol 4–8 mg/kg/h, with scheduled replenishment of sufentanil and cis-atracurium. Heparin 300 IU/kg is given intravenously at the beginning of the operation, and esmolol is administered to patients in the intervention group after the activated clotting time reached > 480 s. Esmolol will be administered by a single-dose bolus (usually 500 μg/kg) followed by a continuous infusion (between 100 and 300 μg/kg/min or titrated in order to maintain low heart rates). Patients in the control group will receive extracorporeal circulation and the surgical operation is completed, and 300 mg of amiodarone is then administered 10 min before aortic opening. Drug infusion is stopped 10 min after opening the aorta in both groups. If electrical defibrillation is required after aortic opening, defibrillation is initially performed using 20 J, and if this is ineffective twice, defibrillation is repeated using 30 J. If defibrillation is unsuccessful after 3 attempts, a second dose of study medication will be administered on the basis of prior randomization. Patients in the control group will receive an additional 150 mg of amiodarone. At the end of the procedure, the patient will be returned to the cardiac surgery unit under ventilatory ball-assisted ventilation.

A five-lead electrocardiogram, ambulatory blood pressure, oxygen saturation, end-expiratory CO_2_ pressure, BIS, and nasopharyngeal temperature will be monitored throughout the procedure and blood gas analysis will be performed at regular intervals.

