#### Secondary outcome measures

The secondary outcomes are the energy and frequency of electrical defibrillation, pacemaker use, anesthesia time, CPB time, aortic occlusion time, and operation time in the two groups.

The other data are heart rate, mean arterial pressure (MAP), and central venous pressure (CVP) at the time of anesthesia induction (T1), surgery (T2), cardiopulmonary bypass (T3), aortic occlusion (T4), aortic opening (T5), after opening for 10 (T6), 20 (T7), and 30 min (T8), at cessation of cardiopulmonary bypass (T9), and completion of surgery (T10). Blood gas analysis results at T1, T5, T9, and T10 are also recorded and compared (Fig. 1).

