### Determination of sample size

We determined the required sample size based on the prevalence of VF as the primary outcome. A previous retrospective study found that the incidences of VF are 39% [11] and 23% [12] in patients treated with amiodarone or esmolol, respectively, prior to aortic opening. A sample size of 127 patients per group is appropriate to finish the trial to detect a difference with 80% power and a 5% type I error rate. Given the potential for patient dropouts, a sample of 130 patients per group is required.

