### Statistical analysis

Statistical analysis will be performed using SPSS software, version 26.0 for Windows (SPSS, Inc., Chicago, IL, USA). Continuous variables will be described as mean (standard deviation) or median (25% and 75% percentile) and will be analyzed using independent *t*-tests or Mann–Whitney *U*-tests, respectively. Categorical variables will be described as a frequency or percentage and will be analyzed by *χ*^2^ tests. Prior to statistical analysis, each continuous variable will be analyzed to determine if it is normally distributed. If the assumption of a normal distribution is violated, the appropriate transformation will be used.

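### Heart rate, arterial pressure and venous pressure would be tested separately at up to ten time points, some before any study drug, ignoring repeated measures and baseline (minor; primary outcome unaffected)

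*Protocol article*

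**What the plan says.** The abstract (Methods/design) commits to between-group comparison: the investigators will "compare the heart rate, mean arterial pressure, and central venous pressure between the two groups of patients at induction of anesthesia (T1") and at each later point through T10. Secondary outcome measures repeats the list but classes these readings as other data, apart from the primary and secondary outcomes. It adds: "Blood gas analysis results at T1, T5, T9, and T10 are also recorded and compared".

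The only method given for such data is in Statistical analysis: "Continuous variables will be described as mean (standard deviation) or median (25% and 75% percentile"), with independent t-tests or Mann-Whitney U-tests respectively, and a transformation where normality fails. That section names no repeated-measures method, baseline adjustment or multiplicity rule, and does not mark these comparisons as descriptive. The section on non-adherence and missing data mentions a main analytical model with covariates, but only for a missing-data sensitivity analysis. Statistical analysis defines no such model.

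On drug timing, General anesthesia starts esmolol after heparin, once the activated clotting time exceeds 480 s. In the control group, "300 mg of amiodarone is then administered 10 min before aortic opening". Infusion stops in both groups 10 min after opening (T6). The Participant timeline table marks both drugs in the T4 column only.

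**The concern.** Ten readings of one variable on one patient are not ten separate experiments. Testing each time point alone ignores the patient's own starting value and gives no overall answer on whether the arms differ. It also gives the reader no rule for discounting an isolated significant time point.

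Some of the time points cannot answer the trial's question. Before any drug is given, randomised arms differ only by chance, so a p-value there says nothing about treatment. Between the start of esmolol and the start of amiodarone, the contrast is esmolol against no study drug yet given. Esmolol may be titrated to keep heart rate low, so a real heart-rate difference is expected in that interval, but it is not esmolol against amiodarone.

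At stake is how the haemodynamic and blood gas results are read, not the conclusion on ventricular fibrillation.

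**Working it through.** **1. The plan's own figure.** The plan gives no error rate for these comparisons. Its only stated error rate is in Determination of sample size: "detect a difference with 80% power and a 5% type I error rate". I take 5% two-sided as the level for each test; sidedness is not stated.

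That section's sample size reproduces closely. With "the incidences of VF are 39% [11] and 23% [12] in patients treated with amiodarone or esmolol":
- Pooled variance (mean rate 0.31): n = [1.960 x sqrt(2 x 0.31 x 0.69) + 0.842 x sqrt(0.39 x 0.61 + 0.23 x 0.77)]^2 / 0.16^2 = 130 per group.
- Unpooled variance: 0.415 x (1.960 + 0.842)^2 / 0.16^2 = 127.2, or 128 rounded up.

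The stated 127 is consistent with this, so a two-sided 5% level is a fair reading.

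**2. Number of tests.** Heart rate, mean arterial pressure and central venous pressure at T1-T10: 3 x 10 = 30. Blood gases add four tests per item; the number of items is not stated, so they are left out of the count.

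**3. Which tests compare the two drugs** (General anesthesia text)
- T1 and apparently T2: before any study drug. 3 x 2 = 6 tests.
- T4, probably also T3: amiodarone not yet given. 3 to 6 tests.
- T5-T10: both drugs started. 3 x 6 = 18 tests.

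So 9 to 12 of the 30 tests do not set esmolol against amiodarone.

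**4. Ceiling on the false-positive chance.** If all 30 nulls are true and the tests are independent, 1 - 0.95^30 = 0.785. The expected number of false positives is 30 x 0.05 = 1.5; this does not depend on correlation but does need all nulls true. The six T1-T2 tests alone give 1 - 0.95^6 = 0.265. Leaving out T3 and T4, where a real heart-rate effect is expected, gives 1 - 0.95^24 = 0.708.

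**5. Allowing for correlation.** The documents give no within-patient correlation, so a range was assumed. Null z statistics were simulated (80,000 runs per setting) with equal or first-order autoregressive correlation over time, and correlation 0 or 0.3 between variables. Chance of at least one p < 0.05:

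| Assumed correlation over time | 30 tests | 24 tests (T3, T4 out) |
|---|---|---|
| 0.5 | 62-74% | 56-65% |
| 0.7 | 49-66% | 45-58% |
| 0.9 | 32-46% | 30-41% |

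The 24-test column treats the eight times as consecutive, so its autoregressive values are approximate.

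**6. Gain from the baseline.** Adjusting for T1 multiplies residual variance by 1 - rho^2. At an assumed rho of 0.5 this is 0.75, a 25% reduction.

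**7. Text against table.** General anesthesia starts the drugs at different times and continues infusion to T6. The table marks both under T4 alone. T1 is before treatment, and T5 is after both drugs have started, on either version; the status of T3 and T4 is not settled.

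**The case against.** The strongest defence is one of status. These are other data. The sample size and the trial's stated purpose rest on one primary outcome, whose type I error these tests do not touch. That stands, and it limits the point to minor.

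A reader might infer that the plan carries a 79% chance of a false haemodynamic finding. The documents do not support that. The figure needs independent tests, but these are repeated readings on the same patients. It also needs every null to be true, and esmolol titrated on heart rate makes a real difference likely at T3-T4. Nor do they say that a significant time point would be presented as a difference between the drugs.

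A second defence is that Statistical analysis is a general paragraph and that modelling detail may sit in an analysis plan that is not shown. It is true that no sentence describes ten separate tests per variable; that reading joins two sections. But the objection here is to the method the article does state, which does not suit the comparisons it announces.

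Third, T3-T4 can be defended as a valid randomised comparison of two regimens with different start times. That is fair, but it is not a comparison of the two drugs once both are given.

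Fourth, the amiodarone mark under T4 can be read as the interval from occlusion to opening. That is possible; the esmolol mark is harder to square with the text.

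Finally, heart rate at T5, the moment of aortic opening, may not suit a linear model. The fix allows for this.

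**Conclusion.** The point holds as a minor one. As written, the plan implies up to 30 separate two-sample tests of haemodynamic readings, plus blood gases at four times, using neither the repeated structure nor the baseline. Six of the 30 (T1 and apparently T2) can show only chance differences. Three to six more (T4, probably T3) compare esmolol with no study drug yet given.

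The chance of at least one false difference is at most about 79%, and roughly 32-74% at assumed within-patient correlations of 0.9 to 0.5 with all nulls true. Even the lowest value is about six times 5% (0.32 / 0.05 = 6.4). The drug-timing counts rest on the General anesthesia text rather than the table. The primary ventricular fibrillation analysis is unaffected.

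**What to change.** - For each of heart rate, mean arterial pressure and central venous pressure, fit one repeated-measures (mixed) model to T5-T10, with arm, time, arm-by-time and the T1 value as covariate. Make one joint test of arm (main effect and interaction together). If the T5 heart rate is not meaningful at aortic opening, start that model at T6.
- Do the same for each blood gas item at T5, T9 and T10, with T1 as covariate.
- Show T1-T4 descriptively, without p-values.
- Label all these analyses exploratory. Three joint tests still carry up to 1 - 0.95^3 = 14% if independent and null.
- Reconcile the drug timing in General anesthesia with the Participant timeline table, so that the document is clear about which readings precede each drug.

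The cost is a change of analysis wording and a correction of the timing inconsistency. No new data or patients are needed, and the models run in the named software. If the team wants no modelling, labelling every one of these comparisons descriptive and dropping the T1-T2 tests is a smaller change that removes most of the problem but leaves the baseline unused.

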**Discussion:**

This study will determine if prophylactic esmolol is more effective than amiodarone for reducing the incidence of reperfusion ventricular fibrillation in patients undergoing heart valve or aortic surgery.

**Trial registration:**

China Clinical Trials Registry ChiCTR1900026429. Registered on 2019.10.9.

## Background

Advancements in surgical methods, aids, and cardiopulmonary bypass (CPB) techniques have increased the indications for open heart surgery. However, cardiac surgery and CPB are still associated with potentially fatal consequences, such as bleeding, infection, and arrhythmias. Arrhythmias are the most severe complication, and ventricular fibrillation (VF) is the most severe secondary arrhythmia [1, 2], with reperfusion VF occurring in 70–96% of cases of CPB [3, 4]. Pathophysiologically, VF is associated with aortic opening-induced myocardial ischemia and reperfusion injury, together with the ensuing inflammatory reactions, oxidative stress, and electrical instability [5]. Electrical defibrillation has been the gold standard treatment for VF after aortic opening; however, electrical defibrillation may aggravate myocardial damage and lead to cardiac dysfunction, as well as recurrent and fatal arrhythmias [6]. Preventive measures are therefore needed to reduce the risk of VF after aortic opening during open heart surgery and improve patient outcomes.

Antiarrhythmic medications have been shown to be effective for treating VF following aortic opening during cardiac surgery, with amiodarone and esmolol chosen as the representative medicines for clinical use. As a class III antiarrhythmic medication, the main electrophysiological mechanism of amiodarone involves lengthening the action potential and effective refractory period of cardiac tissue, hence preventing return-excitation. Amiodarone also slows the conduction rate by inhibiting the fast influx of sodium ions into the conduction fibers of the atria and myocardium. However, its ability to prevent VF is inconsistent [7, 8]. Esmolol is a selective beta 1 blocker with a very short half-life, which has been shown to accelerate spontaneous cardiac recovery following aortic opening and decrease the incidence of reperfusion VF [9].

Their pharmacological properties and past research suggest that both amiodarone and esmolol can successfully prevent and cure reperfusion VF following CPB. We hypothesized that esmolol would be more effective in this regard, and accordingly designed a clinical trial to compare the efficacies of amiodarone and esmolol for preventing reperfusion VF during open heart surgery.

## Methods/design

### Study design {8}

This is a prospective single-center, double-blind, superiority randomized controlled clinical trial to compare the efficacies of amiodarone and esmolol for preventing reperfusion VF during open heart surgery in patients undergoing heart valve or aortic surgery.

Amiodarone has been shown to increase survival, improve hemodynamic parameter maintenance, and reduce myocardial damage in an experiment by Zoerner et al. during direct cardiac surgery [10]. Exogenous epinephrine has long been acknowledged as a crucial medication for cardiac resuscitation despite the significant release of endogenous catecholamines during VF. Post-defibrillation dysfunction and arrhythmias are more likely to happen when the heart’s metabolic needs have increased and its energy reserves are depleted. Exogenous epinephrine also affects cardiac control by altering the activity of the cardiac nervous system. Esmolol, an ultrashort-acting beta-adrenergic receptor blocker, has been demonstrated to drastically lower hypertension, tachycardia, and arrhythmias brought on by intubation and surgical stimulation when administered as a preventative measure in patients having coronary artery surgery. The effects of these two commonly used drugs have rarely been compared.

## Study site and patient selection

### Patients

A total of 260 patients who underwent heart valve or aortic surgery at the Department of Cardiac Surgery, The First Affiliated Hospital of China Medical University, Shenyang, Liaoning province, China, starting November 1, 2019, are recruited. The purpose and potential risks and benefits of the study are fully explained to the patients and their families before surgery, and informed consent will be obtained.

### Inclusion and exclusion criteria

The inclusion criteria are ASA class II to III and a signed informed consent form. The exclusion criteria are an allergy to amiodarone or esmolol, history of bronchial asthma, history of thoracotomy, history of malignant arrhythmia, and abnormal liver, kidney, or thyroid function.

### Who will take informed consent? {26a}

Informed consent is obtained from the anesthetist during the pre-operative visit or from the blinded members of the study team on the day of surgery. Written informed consent is also required from the patient’s legal representative and the investigator before any study-related procedures are started (26a).

### Additional consent provisions for collection and use of participant data and biological specimens {26b}

Not applicable, collection of biological samples is not required.

### Recruitment {15}

In addition to being examined at the preoperative visit, any patient getting ready for heart surgery must schedule an anesthetic evaluation exam at our facility’s anesthesia clinic. The anesthesiologist will describe the trial and respond to any queries from the parents or legal representative during the session.

The researcher will thoroughly explain to participants the research questions, the advantages of the protocol, and the positive impact of the inquiry on public health in order to encourage them to actively participate throughout the study. Additionally, subjects will be urged to be accessible afterwards to call the investigator for counseling and medical guidance based on trial-related biochemical signs. Free medical services will be provided at each visit enquiry, while these services are not required.

## Interventions

### General anesthesia

All patients will receive conventional general anesthesia as follows: induction with midazolam 0.05 mg/kg, etomidate 0.3 mg/kg, sufentanil 0.5 µg/kg, and cis-atracurium 0.2 mg/kg. The anesthesia machine is connected after tracheal intubation, the tidal volume is set at 6–8 mL/kg, and the respiratory rate is 12 breaths/min. The intraoperative end-tidal CO_2_ pressure is maintained at 35–45 mmHg by adjusting the respiratory parameters, and the bispectral index (BIS) is maintained at 40–60. Anesthesia will be maintained with continuous pumping of propofol 4–8 mg/kg/h, with scheduled replenishment of sufentanil and cis-atracurium. Heparin 300 IU/kg is given intravenously at the beginning of the operation, and esmolol is administered to patients in the intervention group after the activated clotting time reached > 480 s. Esmolol will be administered by a single-dose bolus (usually 500 μg/kg) followed by a continuous infusion (between 100 and 300 μg/kg/min or titrated in order to maintain low heart rates). Patients in the control group will receive extracorporeal circulation and the surgical operation is completed, and 300 mg of amiodarone is then administered 10 min before aortic opening. Drug infusion is stopped 10 min after opening the aorta in both groups. If electrical defibrillation is required after aortic opening, defibrillation is initially performed using 20 J, and if this is ineffective twice, defibrillation is repeated using 30 J. If defibrillation is unsuccessful after 3 attempts, a second dose of study medication will be administered on the basis of prior randomization. Patients in the control group will receive an additional 150 mg of amiodarone. At the end of the procedure, the patient will be returned to the cardiac surgery unit under ventilatory ball-assisted ventilation.

A five-lead electrocardiogram, ambulatory blood pressure, oxygen saturation, end-expiratory CO_2_ pressure, BIS, and nasopharyngeal temperature will be monitored throughout the procedure and blood gas analysis will be performed at regular intervals.

### Strategies to improve adherence to interventions {11c}

To encourage better study compliance, the researcher will thoroughly explain the trial to each patient and give them instructions for taking both medications. If any concerns or health problems arise while they are subjects in the study, the researcher will get in touch with them. Since the focus of this pilot project is perioperative indicators, it is unique that the investigator will carry out the majority of the experimental procedures, ensuring a particular level of adherence.

### Relevant concomitant care permitted or prohibited during the trial {11d}

Not applicable. If it is a necessary therapeutic intervention to preserve the patient’s life, it will not be discontinued. Groups that do not fit the trial’s primary study criteria may be excluded.

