### Outcome {12}

#### Primary outcome measure

The main outcome is the incidence of VF following aortic opening within 30 min during extracorporeal circulation.

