### The treatment of non-adherence and missing data {20c}

Analyses will be performed with intention-to-treat: all participants will be analyzed according to the block to which they are randomly assigned. In addition, the trial includes the intraoperative administration of two drugs and the monitoring of intraoperative-related data. The amount of data lost is expected to be minimal.

The researchers will make every effort to collect all follow-up data on all participants, and almost all data will be collected in the perioperative period. Therefore, it is expected that missing data will be minimal. Subjects with missing co-primary outcome data will not be included in the primary analysis in the first place. Each randomized group’s result data is summarized separately. By comparing baseline characteristics of subjects with missing and imputed values, potential bias owing to missing data will be examined. Missing predictors can be identified using the number of missing values. The missing predictors will subsequently be included as covariates in the main analytical model via a sensitivity analysis. Various multiple interpolation algorithms can also be used if necessary.

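### An undefined exclusion clause under care during the trial, and a complete-case rule, both contradict the statement that all randomised patients are analysed

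*Protocol article*

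**What the plan says.** Three statements in the Protocol article bear on who enters the primary analysis.

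- **Concomitant care {11d}.** After marking the item as not applicable, the section says of life-preserving treatment: "If it is a necessary therapeutic intervention to preserve the patient’s life, it will not be discontinued". The next sentence is: "Groups that do not fit the trial’s primary study criteria may be excluded". The article does not define the criteria meant, who decides, when, or whether exclusion is from treatment or from the analysis.
- **Non-adherence and missing data {20c}, analysis set.** The analysis is by intention to treat: "all participants will be analyzed according to the block to which they are randomly assigned".
- **Same section, missing outcomes.** "Subjects with missing co-primary outcome data will not be included in the primary analysis in the first place". The section also says "The amount of data lost is expected to be minimal". It plans a comparison of baseline characteristics and a covariate sensitivity analysis, and adds: "Various multiple interpolation algorithms can also be used if necessary".

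The outcome section names one primary outcome: "The main outcome is the incidence of VF following aortic opening within 30 min during extracorporeal circulation". The participant timeline puts random allocation at T0, before surgery.

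**The concern.** The exclusion sentence is not in the eligibility section. It sits under care during the trial, which here means care given in theatre after allocation at T0. Read where it stands, it gives discretion to remove randomised patients on criteria the article does not define. That conflicts with the promise to analyse all participants as randomised. The complete-case rule conflicts with the same promise, to the extent that any outcome is missing.

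An exclusion made after randomisation can depend on what happened after randomisation. If it were related to VF, the observed rates would no longer be those of the randomised groups. If it also differed between arms, the comparison itself would be biased, in either direction. Readers of the results could not tell whether this had happened, because no rule was fixed in advance.

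**Working it through.** **1. Statements side by side**

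| Section | What it does to the primary analysis set |
|---|---|
| {20c}, first statement | Keeps every randomised participant in the assigned arm |
| {11d}, third sentence | Allows undefined groups to be excluded, at an unstated time |
| {20c}, second statement | Removes patients without the primary outcome |

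The second and third rows each subtract from the first. The timeline places allocation before all intraoperative care, so an exclusion prompted by that care comes after randomisation.

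**2. The plan's own figure**

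Inputs from the sample size section: 39% (amiodarone), 23% (esmolol), 80% power, 5% type I error, 127 per group raised to 130. Two-sided testing is assumed, as sidedness is not stated. The two-proportion formula gives 128 per group unpooled and 130 pooled, so 127 is reproduced within rounding and choice of method.

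Power at 130 per group = Φ[(d − 1.96·SE0)/SE1], where SE0 uses the pooled rate and SE1 the separate rates:

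- d = 0.16; SE0 = √(0.31 × 0.69 × 2/130) = 0.0574; SE1 = √[(0.39 × 0.61 + 0.23 × 0.77)/130] = 0.0565
- (0.16 − 0.1124)/0.0565 = 0.84, so power is 80.0%.

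The allowance for dropout is 3 of 130 per arm, or 2.3%.

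**3. Illustration of selective exclusion (fractions assumed; the documents give none)**

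If a fraction f of VF patients is removed from an arm with true rate p, the observed rate is p(1 − f)/(1 − pf) and the arm keeps 130(1 − pf) patients.

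*Both arms, true rates 39% and 23%:*

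| f | Observed rates | Difference | Patients kept | Power |
|---|---|---|---|---|
| 0 | 39.0% vs 23.0% | 16.0 points | 130 / 130 | 80.0% |
| 10% | 36.5% vs 21.2% | 15.3 points | 124.9 / 127.0 | 77.0% |
| 20% | 33.8% vs 19.3% | 14.6 points | 119.9 / 124.0 | 73.3% |

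*One arm only, no true difference (31% in both, the mean of the two planning rates):*

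| f | Patients removed | Rate in that arm | False difference | Type I error |
|---|---|---|---|---|
| 0 | 0 | 31.0% | 0 | 5.0% |
| 10% | 4.0 | 28.8% | 2.2 points | 6.7% |
| 20% | 8.1 | 26.4% | 4.6 points | 12.5% |

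For the last row, d = 0.0456, SE0 = 0.0571 and SE1 = 0.0569. The two tails are Φ(−1.16) = 0.122 and Φ(−2.77) = 0.003, together 0.125.

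**4. Missing outcomes, with 3 per arm (the dropout allowance, used here as an assumption)**

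The worst case counts the missing as VF on esmolol and no VF on amiodarone. P-values are Pearson chi-square without continuity correction.

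- Near the planning rates: 50/127 vs 29/127 gives p = 0.004. The worst case, 50/130 vs 32/130, gives p = 0.016, still significant.
- A borderline table: 48/127 vs 33/127 gives p = 0.043. The worst case, 48/130 vs 36/130, gives p = 0.11.

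So the missing-outcome rule matters only if the result is close to the threshold.

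**The case against.** A reader might infer that the plan allows exclusion because of life-saving treatment, and so loses the patients who fibrillate. The documents do not support that.

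- The sentence on life-preserving treatment protects that care and does not mention exclusion. The link comes only from the two sentences standing next to each other. The undefined criteria could also mean the eligibility criteria.
- VF is the primary outcome. Its treatment is part of the planned procedure ("If electrical defibrillation is required after aortic opening, defibrillation is initially performed using 20 J"), and the energy and frequency of defibrillation are secondary outcomes. The plan sets out to collect data on these patients.
- A patient seen to fibrillate within 30 minutes has a recorded outcome, so the missing-outcome rule does not remove that patient. It would more plausibly affect someone who dies or is withdrawn before 30 minutes without observed VF.
- The allocation and blinding sections state that the anesthesiologist and the outcome assessor do not know the assignment. Arm-dependent exclusion cannot be presumed from this text.

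Complete-case analysis is also defensible where almost no data are missing, and the plan adds a baseline comparison, a sensitivity analysis and optional imputation. Making multiple imputation the primary method would be a preference. Co-primary is a wording slip, since only one primary outcome is named.

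All of this stands. It removes the claimed mechanism but not the contradiction. If the clause means eligibility before randomisation, it is in the wrong section and should say so. If it means anything later, it conflicts with the intention-to-treat statement.

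**Conclusion.** The point holds as an internal contradiction with a possible bias. An undefined, discretionary exclusion, placed under care during the trial, and a complete-case rule both conflict with the promise to analyse all participants as randomised. It is a should-fix.

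The size of any bias cannot be derived from the documents. The figures of 73% power (20% of VF patients removed from both arms) and about 12.5% type I error (20% removed from one arm, both true rates 31%) rest on assumed fractions. Those fractions mean about 10 and 6 exclusions in the first case and 8 in the second, more than the 3 per arm allowed for dropout. They show what an unrestricted clause could do; they are not a forecast. The missing-outcome rule has little effect at the planning rates and could decide only a borderline result.

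**What to change.** 1. Delete the exclusion sentence in {11d}, or limit it explicitly to eligibility before randomisation.
2. State in {20c} that no randomised patient leaves the primary analysis because of care or events after randomisation, and that every patient with an observed VF outcome is analysed in the assigned arm.
3. Add a best-case and worst-case sensitivity analysis for any missing VF outcome: missing counted as VF in one arm and no VF in the other, then reversed.
4. Replace co-primary with primary.

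The cost is a few sentences and one extra sensitivity analysis. Sample size and data collection are unchanged.
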